### 2.5. Harms

Risk assessment and mitigation strategies will be analyzed and implemented both before and during the trial. Safety and adverse events associated with the groups will be monitored throughout the intervention and reported to the ethics committees if serious. All identified unintended effects or adverse events will be recorded by the research team according to standard guidelines and reported to the ethics committee.

### 2.6. Outcome Measures

#### 2.6.1. Primary Outcome Measures

36-item Short Form Health Survey (SF-36) version 2

This instrument assesses general health in eight domains: physical function, role physical, bodily pain, general health, vitality, social function, role emotional and mental health. Scores above or below 50 (the normative score from the general population) are interpreted as better or worse than the reference population, respectively. This questionnaire has a high validity and test–retest reliability [28].

Fugl-Meyer Upper Extremity Assessment Scale (FM-UE)

The FM-UE is a performance-based index used to assess motor impairment in the upper extremities. It assesses movement of the biceps, triceps, shoulder, elbow, forearm, hand, wrist and finger by performing of 33 tasks. Clinicians rate the patient’s performance on each task for quality of movement on a scale from 0 (no active movement) to 2 (movement appears normal). The maximum score is 66 points, and a high score indicates less impairment. The FM-UE has excellent psychometric properties, including high inter-rater reliability and excellent test–retest reliability and responsiveness [29].

#### 2.6.2. Secondary Outcome Measures

Ten-Meter Walk Test (10MWT) (Gait Velocity)

The 10 MWT is used to assess walking mobility and endurance by measuring walking speed in meters per second over a short distance, and it is calculated as distance divided by time. The patient is instructed to walk at a self-selected speed using any walking aids that may be required. Although there is evidence of excellent internal consistency and test–retest reliability of the test in patients with chronic stroke, there is little evidence of responsiveness in this population. Evidence for validity is also limited but can be inferred from its association with community walking [30].

Six-Minute Walk Test (6MWT) (Gait Endurance)

The 6MWT is used to assess aerobic capacity and endurance. The distance covered in 6 min is used as the outcome to compare changes in performance capacity. It is measured in meters, so the more meters the user is able to cover, the more distance and “normal functioning” will be recorded. The 6MWT has good test–retest reliability in older people and in acute stroke. However, the test has clear face validity in patients with chronic stroke [31].

Timed Up and Go (TUG)

The TUG is used to assess the ability to perform sequential motor tasks related to walking and turning. This test is scored on a scale of seconds measured, with less than 10 s being considered as “functional independence” and more than 30 s being considered “severely abnormal function”. The test–retest reliability of the TUG is high according to previous studies in people with stroke [32].

Berg Balance Scale (BBS)

This scale is a 14-item measure of functional balance, where each item is a five-point ordinal scale ranging from 0 to 4, with 0 representing the lowest level of function and 4 representing the highest level of function. Scores can range from 0 to 56. The higher the score, the better the postural control. The BBS has good internal consistency, confidence interval and test–retest reliability [33].

Global Physical Activity Questionnaire (GPAQ)

This tool consists of 19 questions grouped to capture physical activity across different behavioral domains in which physical activity is performed. It is scored in minutes per day to provide meaningful behavioral units. The GPAQ had low to moderate validity for total PA when compared with PA monitoring questionnaires or accelerometers, and good test–retest reliability [34].

In addition, a physiotherapist will conduct a comprehensive clinical examination to determine whether participants have any physical conditions that may affect their ability to perform certain activities and require adaptations. Participants in both groups will also complete an exercise diary documenting the duration, type and modality (aerobic, strength, flexibility) of their session, which will serve as an additional measure.

#### 2.6.3. Sociodemographic and Anthropometric Data, and Comorbidities

A general screening questionnaire will be used to inquire about possible factors influencing outcomes and to collect baseline information about the sample. Sociodemographic data (date of birth, sex, and school type) and anthropometric data (weight and height to report body mass index (BMI) in kg/m^2^) will be requested, as well as medical diagnoses and comorbid conditions (e.g., controlled epilepsy or asthma medication).

### 2.7. Study Timeline

All participants will attend baseline assessments (post-allocation, T1) prior to randomization into the groups and will be re-assessed at the end of the study period after 8 weeks (close-out, T2). The study schedule is shown in Table 3.

### 2.8. Sample Size

Based on a review of the literature [35,36], people who undergo an exercise therapy program show improvements such as improved quality of life and functionality. Therefore, the sample size was calculated based on the primary outcomes: SF-36 and FM-UE.

Previous studies have shown that a difference of 12.4 points with an SD of 5 points in the FM-UE score is required to detect the minimum clinically important difference between the two study groups [37,38].

Furthermore, Norman et al. conclude that the threshold for detecting changes in health-related quality of life is approximately 5 points [39]. Taking into account the possible number of subjects we could recruit, the sample size is calculated to detect an improvement of 5 points in the summary components of the SF-36 questionnaire with a standard deviation (SD) of 5 points. The SD value was taken as half that of the general population (SD = 10) because we considered our sample to be more homogeneous. To detect this difference between the groups with a 95% confidence interval and 80% power for a bilateral approach, we would need 16 subjects. If we estimated a 15% attrition rate, the final sample size would be 18 subjects in each group.

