## 1. Introduction

Acquired brain injury (ABI) constitutes a significant and growing global public health concern. ABI is a disorder of the mature brain, regardless of its severity or duration, resulting from various etiologies, including stroke, traumatic brain injury, tumors, or infectious diseases [1,2].

People with ABI often face a range of physical and psychosocial challenges, spanning all domains of the International Classification of Functioning, Disability and Health (ICF) model. They experience impairments in the area of “body structure and function” domain (e.g., spasticity, muscle weakness, or poor motor control). In addition, these impairments can have a ripple effect, limiting their abilities within the “activity” domain (e.g., difficulties with fine motor function) and also affecting the “participation” domain (e.g., reduced physical activity and participation in sport) [2]. These patients may experience a reduced physical functioning and health-related quality of life, as well as impaired active participation in community-based physical activity and sports [3,4]. Therefore, the ICF is an important biopsychosocial framework to consider when designing and implementing rehabilitation programs for people with disabilities [5,6]. Hence, evidence suggests that effective rehabilitation interventions for people with ABI should include improvements in all domains [6,7].

Numerous studies have highlighted the positive outcomes of exercise therapy programs for people with ABI. Based on motor learning principles, several systematic reviews have consistently demonstrated the activation of supplementary motor areas and more consistent functional recovery compared to usual care alone [8,9,10,11,12]. In terms of design, multidisciplinary approaches that emphasize the integration of exercise therapy with social leisure activities are considered essential to elicit neuroplastic adaptations that enhance physical recovery [11,13,14,15], and address cognitive and behavioral sequelae following ABI [16,17]. In addition, group-based therapy programs with fewer participants per session have positively affected ABI patients’ quality of life, self-esteem, and social inclusion, as this format encourages and maximizes extensive patient interactions [18,19,20,21].

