### 2.10. Statistical Methods

The comparability of the study groups will be assessed by the similarity of the distribution of the variables of interest at baseline. The analysis will follow standard methods for randomized controlled trials, using two-group comparisons for all participants on an intention-to-treat basis. The chi-squared test or Fisher´s exact test will be used to compare proportions. Student´s *t*-test will be used to compare means between groups with normally distributed data. The Mann–Whitney test will be used to compare quantitative variables between groups in the case of a non-normal distribution, as determined by the Kolmogorov–Smirnov test. Correlations between quantitative measures will be determined by Spearman’s rho correlation coefficient. Matched pair data analysis is also calculated. In addition, multivariate analysis will be performed using multiple linear regression and logistic regression, depending on the response under consideration. This will allow for adjustment of the effectiveness of the intervention for potential confounders and the identification of other variables associated with each of the outcomes. Statistical significance will be set at ≤0.05. Data will be analyzed using the Statistical Package for the Social Science (SPSS) software, version 27.0 (IBM Corp, Armonk, New York, NY, USA).

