## Figures and Tables

**Figure 1 jcm-12-07068-f001:**
[figure not shown]
Flowchart of the study design.

**Table 1 jcm-12-07068-t001:** Eligibility criteria.

Inclusion Criteria	Exclusion Criteria
Persons with a medical diagnosis of an acquired brain injury in the subacute or chronic stage (within more than one month of the injury).	Do not have a completed and signed informed consent form.
Be aged >18 years at study entry.	Failure to attend and/or participate in 70% of the program sessions.
To walk independently without the use of assistive devices: score of ≥3, 4 or 5 on the Functional Ambulation Categories (FAC) walking test.	Have medical comorbidities that contraindicate safe exercise (e.g., cardiac or respiratory instability, and uncontrolled seizures).
Be able to understand simple instructions from the exercise therapy program and carry out baseline and post-intervention assessments.	Failure to cooperate during the preliminary tests of the program.

**Table 2 jcm-12-07068-t002:** Template for intervention description and replication checklist for the intervention.

TIDieR Items	Description of Items
Name of the intervention for experimental/comparison group	sET group: racket sports-based exercise therapy program. UC group: usual care
Rationale	Currently, several studies have been carried out that propose a program that combines exercise therapy and adapted physical activity based on different sports (such as basketball or soccer). Nevertheless, no racket sport-based program has been implemented so far. Racket sports emerge as an accessible therapeutic tool with a strong social component that enables the integration of different body synergies and complex motor strategies, thereby promoting functional performance in both the lower and upper limbs. To date, there remains a noticeable gap in the literature regarding exercise programs that comprehensively address all the domains of the International Classification of Functioning, Disability and Health model. This trial raises the need to specifically design exercise therapy programs based on racket sports for this population.
Materials used in the intervention	sET group: The exercise therapy program is centered around different racket sports skills, mainly badminton and tennis, as disciplines which are adapted to participants’ functional condition, as well as different generic equipment such as like balls, chairs, tables, and platforms, among others.

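### Section 2.8's 80% power for SF-36 depends on an SD halved from 10 to 5 without supporting data; over SD 5 to 10 the power runs from 78% to 28%

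*Protocol article*

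**What the plan says.** Section 2.8 (Sample Size) names SF-36 and FM-UE as the primary outcomes behind the calculation. For SF-36 it takes a threshold of about 5 points from a cited source. It opens the calculation with "Taking into account the possible number of subjects we could recruit" and continues: "the sample size is calculated to detect an improvement of 5 points in the summary components of the SF-36 questionnaire". The SD is set at 5 and explained in one sentence: "The SD value was taken as half that of the general population (SD = 10) because we considered our sample to be more homogeneous". The result is given as "with a 95% confidence interval and 80% power for a bilateral approach, we would need 16 subjects", raised to 18 in each group for 15% attrition.

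Three other places bear on the SD:

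- Table 1 (Eligibility criteria) admits "Persons with a medical diagnosis of an acquired brain injury in the subacute or chronic stage", from more than one month after injury with no upper limit, and adults over 18 with no upper age limit. It also requires independent walking without assistive devices (FAC 3 or more) and the ability to follow simple instructions and complete the assessments. It excludes comorbidities that make exercise unsafe.
- The Introduction describes acquired brain injury (ABI) as "resulting from various etiologies, including stroke, traumatic brain injury, tumors, or infectious diseases", whatever its severity or duration.
- Section 2.10 (Statistical Methods) compares groups by t-test, or Mann–Whitney if non-normal, and adds regression to adjust for potential confounders. It does not name the baseline score as a covariate.

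**The concern.** The required sample size grows with the square of the SD, so halving the SD cuts it about fourfold. The halving rests on one sentence of judgement: no pilot SD, no ABI data and no correlation between baseline and follow-up. It stands directly after a remark that recruitable numbers were taken into account. The described population does not obviously vary half as much as the general population on a quality-of-life score.

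SF-36 sets the size of the trial, since FM-UE needs only a handful of patients on the stated inputs. The 80% is stated without conditions. If the SD is nearer the cited value, a non-significant SF-36 result would say little about a 5-point benefit, and a reader relying on section 2.8 could take it as evidence against one.

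**Working it through.** **Inputs.** Difference 5, SD 5, reference SD 10, two-sided 5%, 80% power, 15% attrition and 18 per group are from section 2.8. Allocation 1:1 is from section 2.3. The t-test and the 0.05 level are from section 2.10.

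**Reproducing the plan's figure.** n per group = 2 × (1.96 + 0.84)² × (SD/Δ)² = 15.7 × (5/5)² = 15.7, so 16. The stated 16 is therefore correct per group by the usual normal formula. The exact t calculation gives 16.7, so 17. Power at 16 per group is 80.7% by the normal formula and 78.1% by the t-test. Reading 16 as a total (8 per group) would give only 46% (t-test) to 52% (normal), so 16 must be per group.

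**Which outcome drives the size.** FM-UE: 15.7 × (5/12.4)² = 2.6, so 3 per group (4 by the t calculation). SF-36 governs.

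**Power over a range of SD.** Noncentrality = Δ / (SD × √(2/n)), with 2n − 2 degrees of freedom. For n = 16, √(2/16) = 0.354, so noncentrality is 2.83 at SD 5 and 1.41 at SD 10. The standardised difference detectable with 80% power is 1.024 SD at n = 16.

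| SD | Power, 16 per group | Power, 18 per group (no loss) | Difference detectable with 80% power, 16 per group |
|---|---|---|---|
| 5 | 78% | 83% | 5.1 |
| 6 | 63% | 68% | 6.1 |
| 7.5 | 45% | 49% | 7.7 |
| 8 | 40% | 45% | 8.2 |
| 10 | 28% | 31% | 10.2 |

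The largest SD that keeps 80% t-test power is 5/1.024 = 4.9 with 16 per group, or 5.2 with 18. There is almost no margin above the assumed 5. At SD 10, 80% power would take 15.7 × (10/5)² = 62.8, so 63 evaluable per group (64 by the t calculation).

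**Precision.** With 30 degrees of freedom the critical t is 2.042. The half-width of the 95% interval is 2.042 × SD × 0.354: about 3.6 points at SD 5 and 7.2 at SD 10. At SD 10 an observed difference of zero would leave 5 points inside the interval.

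**Could baseline adjustment supply the SD of 5?** Take an outcome SD of 10 and a baseline-to-follow-up correlation r (assumed; the article gives none). The residual SD is 10 × √(1 − r²). It reaches 5 when r = √(1 − 0.25) = 0.87. Change scores, with SD 10 × √(2(1 − r)), need r = 0.875.

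| Assumed r | Residual SD | Power, 16 per group |
|---|---|---|
| 0.6 | 8.0 | 40% |
| 0.7 | 7.1 | 48% |
| 0.8 | 6.0 | 63% |

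**The case against.** The plan has a fair defence.

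- **The assumption is disclosed.** Section 2.8 gives the SD used, the value it was halved from, the reason and the role of feasibility. Given SD 5, its arithmetic is right; 78% against 80% is only the t-test against the normal formula. This stands: the fault lies in the input and not in the calculation.
- **Some narrowing is documented.** Participants are outpatients of one centre who walk independently, can follow instructions and can exercise safely. A reader might infer that the eligibility criteria contradict an SD of 5. They do not: no statement in the article conflicts with that value, and the list of causes comes from a general definition in the Introduction and not from an entry criterion. What can be said is that the criteria do not support halving, and that nothing stated shows how far they narrow the scores.
- **SD 10 is not an ABI value.** It is the general-population figure, so 28% is one end of a range. This stands.
- **Baseline data may help.** SF-36 is measured at T1 and T2, and section 2.10 plans regression and matched-pair analysis. But the article does not argue that 5 is a residual or change SD; its only reason is homogeneity. Even at an assumed correlation of 0.8, power from an outcome SD of 10 is 63%.
- **The other primary outcome is amply powered.** On the stated inputs FM-UE needs 3 to 4 per group. The problem is confined to SF-36.

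**Conclusion.** The concern holds as one of support and margin. Section 2.8 states 80% power for a 5-point SF-36 difference on an SD that is half the only one it cites, justified by assertion alone. With 16 evaluable per group, t-test power is 78% if the SD is 5, 63% at 6, 45% at 7.5 and 28% at 10 (31% if all 18 per group are retained). The detectable difference runs from 5.1 to 10.2 points, so at the cited SD it is about twice the trial's own threshold.

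It would be tempting to conclude that the trial's power is 28%. The article does not support that: the SD in ambulatory adults with ABI is not given, and baseline adjustment could raise power, to about 48% at outcome SD 10 and an assumed correlation of 0.7. The supportable conclusion is that power is unknown within this range and that the stated 80% sits at its favourable end. These figures assume equal groups, normal data, a two-sided 5% test and a true difference of exactly 5 points.

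**What to change.** Keep the sample size and restate section 2.8:

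1. Remove the homogeneity justification and the unconditional 80% claim. Say plainly that feasibility was a consideration in the calculation.
2. Report power for a 5-point difference over SD 5 to 10 (78% to 28% with 16 evaluable per group, unadjusted) and the difference detectable with 80% power (5.1 to 10.2 points). If baseline adjustment is relied on, state the assumed correlation and show power over a range of it.
3. State that a non-significant SF-36 result will be read from its confidence interval against the 5-point threshold, and not as absence of benefit.

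The cost is rewording and a less favourable stated power. No patients, visits or analyses are added.

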### 2.3. Allocation and Blinding

After completion of the baseline assessment, independent, centralized, stratified block randomization will be used to allocate participants to either the intervention or the control group. Randomization will be performed using a computer-generated random number sequence, with a 1:1 allocation ratio. The assessors involved in eligibility, pre- and post-intervention assessments, and statistical analysis will be blinded to group allocation throughout the entire study period. Due to the nature of the trial, it is not possible to blind intervention parties, including both participant and program staff, to their group assignments.

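### Eighteen per group does not retain the required 16 at 15% attrition, and t-test power on the plan's own inputs is about 75% to 77%, not 80%

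*Protocol article*

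**What the plan says.** Section 2.8 names SF-36 and FM-UE as the outcomes behind the sample size, and the final number comes from SF-36: "the sample size is calculated to detect an improvement of 5 points in the summary components of the SF-36 questionnaire". The SD is set at 5 points, half the general-population value of 10. The requirement is then given as "with a 95% confidence interval and 80% power for a bilateral approach, we would need 16 subjects". This sentence does not say whether 16 is per group, but the next one does so for the inflated number: "If we estimated a 15% attrition rate, the final sample size would be 18 subjects in each group".

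Section 2.3 fixes 1:1 allocation. Section 2.10 says that Student's t-test "will be used to compare means between groups with normally distributed data", with Mann–Whitney if the data are not normal, and "Statistical significance will be set at ≤0.05". The article does not explain how 18 was obtained from 16.

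**The concern.** There are two separate problems, and they add up.

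- **Attrition step.** Neither the correct inflation (divide by 0.85) nor the common shortcut (multiply by 1.15) gives 18 when rounded up. At the stated loss, the planned enrolment falls short of the stated requirement.
- **Base number.** Sixteen per group is what the large-sample formula gives. In groups this small, the t-test named for the analysis needs slightly more.

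The trial presents itself as having 80% power after 15% attrition. If SF-36 shows no significant difference, readers will judge that result against the 80%. In a trial of 36 people, one or two participants per group visibly move the power.

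**Working it through.** **Inputs.** Difference 5, SD 5, two-sided, 80% power, 15% attrition, 18 per group (section 2.8); 1:1 allocation (section 2.3); significance level 0.05 and t-test (section 2.10). The standardized difference is d = 5/5 = 1.

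**Step 1: reproduce the 16.** Normal approximation, per group:

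n = 2 × (1.960 + 0.842)² / d² = 15.70, rounded up to 16.

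The plan's 16 is reproduced, and as a number per group. The same formula gives 80.7% power at 16.

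**Step 2: inflate for attrition.**

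- Correct: 16 / (1 − 0.15) = 18.82, so 19.
- Shortcut: 16 × 1.15 = 18.4, so 19.
- Only rounding 18.4 down gives 18.
- What 18 leaves: 18 × 0.85 = 15.3 per group, or 30.6 in total against the 32 required.
- Loss that 18 can absorb while keeping 16: 1 − 16/18 = 11.1%.
- If each participant is lost independently with probability 0.15, a group of 18 keeps at least 16 with probability 48%, and both groups do so with probability 0.48² = 23%.

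**Step 3: power for the named test.** Two-sample t-test (noncentral t), d = 1, two-sided 0.05, beside the normal approximation:

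| Evaluable per group | t-test power | Normal approximation |
|---|---|---|
| 15 and 15 | 75.3% | 78.2% |
| 15.3 each (expected) | 76.2% | 79.0% |
| 15 and 16 | 76.7% | 79.5% |
| 16 and 16 | 78.1% | 80.7% |
| 17 and 17 | 80.7% | – |

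Averaged over random attrition at 15%, t-test power is 75.8%.

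**Step 4: what 80% would need.** The t-test solution is 16.71, so 17 evaluable per group. 17 / 0.85 = 20.0, so 20 randomized per group (40 in total, against 36 planned).

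**Step 5: the other primary outcome.** For FM-UE (12.4 points, SD 5, d = 2.48), power is above 99.9% at 15 per group. The shortfall concerns SF-36 only.

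**The case against.** The strongest reply concedes that 18 should be 19 and disputes the weight of the rest.

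- **Approximation.** Sixteen is a legitimate normal-approximation result, and its exact t-test power of 78.1% is within 2 points of 80%. On the plan's own formula, the attrition slip alone brings power to between 78.2% and 79.5%, a loss of only 1 to 2 points against the nominal 80%. More than half of the drop to 75.3% comes from switching formula. This stands: the 16 is a choice of approximation, and only the 18 is an arithmetic error. It does not rescue the 80%, which is missed under both methods.
- **Adjustment.** Section 2.10 also plans multiple linear regression, and SF-36 is measured at T1 and T2. If baseline SF-36 were a covariate and the SD of 5 were that of T2 scores, power at 15 per group would be about 79%, 82% and 86% at correlations of 0.3, 0.4 and 0.5. This is a fair caveat. However, the article states no correlation, does not name baseline SF-36 as a covariate, and does not base the calculation on adjustment.
- **Materiality.** The gap is one or two participants per group, and the assumed SD matters far more: at SD 10, t-test power with 15 per group is about 26%. This is true, and it limits the importance of the point. It also means that the calculation shows no slack to absorb the error.

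**Conclusion.** The concern holds. The enrolment of 18 per group is inconsistent with the stated need for 16 at 15% attrition; the correct inflated number is 19. With the t-test of section 2.10, power at the planned attrition is 75.3% to 76.7%, about 76% at the expected 15.3 per group, and 80% would take 20 randomized per group.

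These figures assume a true difference of 5 points, SD 5, an unadjusted t-test at two-sided 0.05 and attrition of exactly 15%. A Mann–Whitney fallback would lower power slightly (about 74% at 15.3 per group, assuming relative efficiency 0.955), and a larger SD would lower it more. Adjustment for a well-correlated baseline would raise it. The shortfall is modest, but it is a definite error in the power statement for the primary outcome that determines the sample size.

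**What to change.** Correct section 2.8 and leave enrolment as it is, which respects the recruitment limit that the section acknowledges. Suggested text: *Eighteen participants per group will be randomized; with 15% attrition about 15 per group are expected to be evaluable, giving about 75% power to detect 5 points at SD 5 with a two-sided t-test at the 5% level.* Using the unrounded 15.3 per group, the figure would be about 76%. The same sentence should say that the 16 is per group.

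If the 80% claim is to stay, section 2.8 should show that it comes from the baseline-adjusted analysis and state the assumed correlation between baseline and T2 scores.

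The cost is one sentence and a stated power about 4 to 5 percentage points lower. Design, enrolment and analysis do not change.
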